**16. APPENDICES**

**Appendix 1. Wound Fluid Collection, Processing, and Storage**

Method taken from A/[name]: SOP-Wound-Fluid-v3-20200212

Purpose

This SOP describes the methodology for the collection and processing of burn wound fluid (WF) samples. Wound fluid samples are opportunistically collected from burn patients who present to the burn centre or emergency department with a burn injury. As part of routine clinical wound cleaning procedures, blisters are de-roofed, and blister fluid is removed and discarded. For this project, instead of being discarded, the blister fluid will be collected, processed and stored so that it can be analysed and used for burn wound healing studies. Additionally, if patients present with an exudating wound, this fluid will be collected instead of discarded. And if patients present with a negative pressure device attached to their wound, and there is fluid in the suction tube, this will also be collected. Samples are ideally received in volumes >100uL, although occasionally less is collected, as sample volumes as small as 50µL can still be analysed using mass spectrometry.

Aim

To process WF specimens and freeze in smaller aliquots to maintain protein quality and prevent repeated free-thawing of samples.

Reagents and Consumables

- Specimen pot 70mL, Sarstedt Cat#75.9922.745 (Polypropylene)
- Whatman Filter paper, sterilised
- Eppendorf Protein Lo-bind tubes Cat#30108094
- Filtered pipette tips
- Pipettes – P200 and P1000
- Microcentrifuge, for 1.5mL to 2.0mL tubes
- Site-specific participant code book or REDCap database
- De-identified wound fluid sample logbook or REDCap database
- Brady label maker Cat#BMP51

Standard Personal Protective Equipment (PPE) must be worn at all times when collecting and processing biological specimens, including gloves and safety glasses during collection and gloves, safety glasses and a laboratory gown when processing the samples in the laboratory. Any staff member or student who is involved in the processing of biological samples must be immunised against Hepatitis B.

Procedure

- 1. During routine wound cleaning procedures, the clinical/nursing team will lance patient blisters and remove any exudating wound fluid. If there is a large volume of fluid (e.g. several mLs,), the fluid can initially be collected in a larger container, such as a specimen pot temporarily.

If the samples are smaller volume, they can be collected directly into the Eppendorf Protein Lo-bind tubes.

If there are multiple blisters on the same patient, these should be collected in separate tubes/pots.

If the patient has a negative pressure device with fluid in the tubing, the tube can be clamped at either end, cut off the device and the fluid from the tube collected in a specimen pot.

If there is only a small amount of fluid, this can be collected with filter paper. The filter paper is placed at the wound edge to absorb the fluid, and then placed into sterile 2mL Lo-Bind tubes.

If a sample is collected in a specimen pot, please transfer to a Lo-bind tube ASAP to prevent protein loss.

- 1. Label the tube/pot with patient UR sticker, the anatomical location of the blister or wound site (e.g. right palm, left thigh) and collection date. **Store in a fridge at 4°C if not processed immediately, and process within 24 hours.**
  2. If the sample is in a specimen pot, transfer it into Eppendorf Protein Lo-bind tube/s ASAP. If you transfer it into multiple tubes (i.e. the volume is greater than 2.0 mL), transfer equal amounts into each tube, so that they will balance in the centrifuge. Label the tube with the participant unique identifier code from your site-specific participant code book or from the REDCap database.

e.g. 49_ 23_ WFa_20190408

(Brisbane Code_ Participant #23_ Wound Fluid__Anatomical Area abcde_Date yyyymmdd)

If the sample is in filter paper, recover the wound fluid by eluting the sample in 100µL of Phosphate Buffered Saline or water at 4◦C for 1 hour (45).

- 1. Centrifuge the sample in a balanced benchtop microfuge for 3 minutes at 855 x x g at ambient temperature to pellet cells and cellular debris.
  2. Record the collection date, anatomical location, total sample volume and any comments on the fluid contents (Blood? Colour? Consistency?) in the WF sample logbook or in the REDCap database.
  3. Without disturbing the pellet, transfer the supernatant to fresh Lo-bind tubes. The volume in each tube should be minimum 50µL, to a maximum of 1000µL. Ensure there are at least 2 aliquots (2 tubes) of each sample. Write the total number of aliquots and aliquot volumes in the WF sample logbook or REDCap database.
  4. Label each aliquot with sample number and date, using the Brady label maker.
  5. Store aliquots in a -80°C freezer.

**Appendix 2. Blood Collection, Processing, and Storage**

Method taken from A/[name]: SOP-Blood-Processing-5-2020200421

Purpose

This SOP describes the methodology for the collection and processing of blood samples. Blood samples are opportunistically collected from burn patients who are undergoing a general anaesthetic for routine burn injury treatments (e.g. dressing change, debridement or grafting). The volume of blood that can be collected from a child depends on their age/size and total blood volume. According to the WHO guidelines for the safe limits of blood volume collection from children, 1-5% of total blood volume can be collected within a 24-hour period, with a maximum of 3mL per kg for sick children. To obtain enough cells to process, collect a minimum of 1mL blood volume, ideally collect around 8-10mL.

Aim

To collect and process blood specimens to obtain Peripheral Blood Mononuclear Cells (PBMC) and plasma. These samples will then be frozen for later analysis.

Reagents and Consumables

- Vacutainers containing lithium heparin (e.g. Becton Dickinson green 10mL Cat #367874)
- Eppendorf Protein Lo-bind tubes Cat#30108094
- Lymphoprep or Ficoll-paque Plus – brought to room temperature
- RPMI containing 20% Heat-inactivated fetal calf serum FCS/FBS – brought to room temperature
- 15mL and 50mL polypropylene tubes
- Sterile, filtered pipette tips
- Pipettes – P200 and P1000
- Electronic pipette aid and serological pipettes (2mL – 25mL)
- Vacuum suction and glass pipettes
- DMSO
- Cryovials, 2ml Corning CLS430659, these cryovials are for LN2 Vapour storage.
- CoolCell/MrFrosty
- Site-specific participant code book or REDCap database
- De-identified blood sample logbook or REDCAP database
- Brady label maker Cat#BMP51

Standard Personal Protective Equipment (PPE) must be worn at all times when collecting and processing biological specimens, including gloves and safety glasses during collection and gloves, safety glasses and a laboratory gown when processing the samples in the laboratory. Any staff member or student who is involved in the processing of biological samples must be immunised against Hepatitis B.

Procedure – Plasma and PBMC

1. Collect blood into vacutainers containing lithium heparin (the BD vacutainers we use specify “17 international units of heparin/mL of blood”). Aim to collect between 8-10mL of blood. Label tube with participant unique identifier code from your site-specific participant code book or REDCap database, and collection date and time.

**Process immediately if possible. Store at room temperature for up to an hour, for longer storage than an hour place in the fridge, and process within 24 hours.**

1. Record the collection and processing date and time in your site-specific participant code book or REDCap database. Centrifuge blood at 400 x g for 10min, brake ON. (400G=1340RPM, where radius=20cm)
2. Aliquot the plasma supernatant into 3-4 x Eppendorf Lo-bind tubes and label these with the unique patient code from your site-specific patient code book or REDCap database, using the Brady label maker.

e.g. 49_23_ P_20190408

(Brisbane Code_Participant #23_Plasma_Date yyyymmdd)

Record the collection date and total plasma volume in the blood sample log book or RedCap database. Store plasma aliquots in a -80 freezer.

Vacutainer Plasma and Blood fractions:

[figure not shown]

Plasma fraction for collection. Do not disturb interphase with RBCs, leave some plasma behind in tube

1. Dilute the remaining blood cells up to 4x in room temperature RPMI+20%FCS. It will probably be necessary to make a 2x dilution first, transfer to a 10 or 15mL tube, then dilute 2x again. * Dilute the remaining cells by first replacing the volume of plasma you removed, i.e. If you removed 4ml of plasma – place 4mls of RPMI & FBS into the remaining blood sample. Secondly, dilute the whole sample 1:1 with RPMI&FBS.
2. Prepare 2 x 15mL tubes by pipetting the correct volume of room temperature Ficoll-paque Plus (or Lymphoprep). See below for volumes (note: use regular 15ml tubes in place of Sepmate tubes):

[figure not shown]

1. Split the diluted blood equally between the two tubes, carefully pipetting down the sides of the tubes.

Blood & Lymphoprep fractions pre-centrifugation

[figure not shown]

1. Centrifuge the sample at 400 x g for 30min at room temperature with the **brake OFF**. (400G=1340RPM, where radius=20cm)

Tubes post spin should look similar to these;

[figure not shown]

[figure not shown]

After centrifugation

Clear PBMC fraction to collect

1. For isolation of the buffy coat layer (containing PBMCs), carefully insert your pipette down the side of the tube and remove out the buffy coat layer. Resuspend into 2 x 15mL tubes.
2. Make each tube up to 15mL with RPMI + 20% FCS. Centrifuge at 500 x g for 10min, brake on. (500G=1500RPM, where radius=20cm).

PBMCs should be a pellet like this:

[figure not shown]

1. Discard the supernatants. Resuspend the pellet from one tube in 1mL of RPMI + 20% FCS and transfer to the other tube. Resuspend the cells in 15mL of RPMI + 20% FCS and centrifuge at 120 x g for 10min, **brake OFF.** This will deplete the platelets from the samples.
2. Discard the supernatant and resuspend the cells in 1mL RPMI + 20% FCS. Take an aliquot for counting.
3. The method used to count the cells is not important as long as it is accurate and allows for live/dead discrimination. We will count by taking a 1:10 dilution of cells, further diluting them 1:2 in 0.4% trypan blue, then counting manually using a haemocytometer.
4. Cells will be stored at approximately 2 x 10^6^ cells/vial. Using the label maker, label enough cryovials with the participant identifier code and place them on ice.

e.g. 49_ 23_ C_20190408

(Brisbane Code_Participant #23_Cells_Date yyyymmdd)

1. Dilute the cells with RPMI + 20% FCS to a concentration of approximately 2 x 10^6^ cells/mL per vial.
2. Place the cells on ice and add an equal volume of pre-chilled RPMI + 15% DMSO; take at least 1min to add the first mL of 15% DMSO drop-by-drop, and slowly add the rest.
3. Transfer aliquots to the labelled cryovials.
4. Move cryovials into a CoolCell/MrFrosty (at room temp) and store in a -80C freezer, at least overnight.
5. Transfer cryovials to liquid nitrogen storage. Write details of the number of cryovials in the blood sample logbook or REDCap Database.

**Appendix 3. Hair Collection, Processing and Storage**

Method based on [name] Protocol 2020

Collecting Hair Samples

1. Separate the hair at the back of the head with a hair clip
2. Collect a hair strand of about 3-5mm and comb
3. Tie up the hair strand with a small hair band/tie or string close to the scalp
4. Cut the hair as close as possible to the scalp
5. Place the hair into the 2ml screw-cap cryo tube

Record Keeping

Record the following in lab book:

1. Patient number
2. Date of sample processing
3. Time of sample processing
4. Name of scientist processing

Hair Storage

Tube should be labelled as follows:

- Patient Number_Sample Date (ddmmyyyy)_H

For example: 1_26032020_H)

- Hair should be stored directly at -80°C

**Appendix 4. Urine Collection, Processing and Storage**

Purpose

This SOP describes the methodology for the collection and processing of urine samples. Urine samples are opportunistically collected from burn patients who present to the burn centre or emergency department with a burn injury. If participants are scheduled to receive a urinary catheter as part of routine standard treatment for their burns, some urine that will be retained for analysis. For participants who do not require a catheter, the child and parent/caregiver will be asked if they consent to providing a urine sample and will be given a urine sample pot container for collection. A minimum volume of 60mL is required for analysis.

Aim

To process urine specimens and freeze in smaller aliquots to maintain protein quality and prevent repeated freeze-thawing of samples.

Reagents and Consumables

- Sterile Specimen pot 250mL, Sarstedt Cat#75.9922.745 (Polypropylene)
- 3 kDa NMWL Amicon® ultra-15 centrifugal filter devices
- Eppendorf Protein Lo-bind tubes Cat#30108094
- Filtered pipette tips
- Pipettes – P200 and P1000
- Microcentrifuge, for 1.5mL to 2.0mL tubes and 50mL tubes
- Site-specific participant code book or REDCap database
- De-identified urine sample logbook or REDCap database
- Brady label maker Cat#BMP51

Standard Personal Protective Equipment (PPE) must be worn at all times when collecting and processing biological specimens, including gloves and safety glasses during collection and gloves, safety glasses and a laboratory gown when processing the samples in the laboratory. Any staff member or student who is involved in the processing of biological samples must be immunised against Hepatitis B.

Procedure

1. A mid-stream urine sample (if possible) will initially be collected in a sterile specimen pot.
2. Label the tube with the participant unique identifier code from your site-specific participant code book or from the REDCap database.

e.g. 49_ 23_ U_20190408

(Brisbane Code_ Participant #23_ Urine_Date yyyymmdd)

1. Freeze the sample at -20^◦^C until processing the next day or later.
2. Thaw the sample in a 25^◦^C water bath, and transfer the sample into multiple 50mL Falcon tubes.
3. Centrifuge the tubes at 1,500 × g for 10 minutes. Collect the supernatant and pass through a sterile 0.2 μm syringe filter to remove any remaining bacterial contamination and high molecular weight protein aggregates.
4. Collect filtrate and concentrate by centrifugation in a pre-rinsed 3 kDa NMWL Amicon® ultra-15 centrifugal filter device, as per manufacturer’s instructions, at 4,000 × g for 30 minutes.
5. Dilute the retentate with 15 mL milli-Q water and centrifuge twice at 4,000 × g for 30 minutes to desalt and remove low molecular weight non-protein components.
6. Following sample concentration, transfer 1mL aliquots of the retentate of each sample into Lo-bind tubes. Label each aliquot with sample number and date, using the Brady label maker.
7. Store aliquots in a -80°C freezer.
8. Write the total number of urine aliquots and aliquot volumes in the sample logbook or REDCap database.

**Appendix 5. Schedule of Assessments**

| Visit | Initial Presentation | COD1 | COD2, COD3…^1^ | Surgical intervention | 3 months | 12 months |
| --- | --- | --- | --- | --- | --- | --- |
| Eligibility and consent |  |  |  |  |  |  |
| Eligibility screen | X |  |  |  |  |  |
| Signed informed consent | X |  |  |  |  |  |
| REDCap data collection forms |  |  |  |  |  |  |
| Demographic and Injury Details | X |  |  |  |  |  |
| Initial Presentation | X |  |  |  |  |  |
| First Change of Dressing |  | X |  |  |  |  |
| Ongoing Dressing Changes |  |  | X |  |  |  |
| Surgical Interventions & Requirements |  |  |  | X |  |  |
| Completion Data |  |  |  |  |  | X |
| Additional data points |  |  |  |  |  |  |
| Time taken to complete dressing | X | X |  |  |  |  |
| % Re-epithelialised | X | X | X | X |  |  |
| Burn depth re-assessment |  | X |  |  |  |  |
| Photos^2^ | X | X | X | X |  |  |
| Pain scales |  |  |  |  |  |  |
| Clinician pain scales – FLACC/NRS^3^ |  |  |  |  |  |  |
| Baseline | X | X | X | X |  |  |
| Peak procedural | X | X | X |  |  |  |
| Parent-proxy pain scales - NRS |  |  |  |  |  |  |
| Baseline | X | X | X | X |  |  |
| Peak procedural | X | X | X |  |  |  |
| Patient pain scales – FACES^4^ |  |  |  |  |  |  |
| Baseline | X | X | X | X |  |  |
| Peak procedural | X | X | X |  |  |  |
| Implementation outcomes^5^ |  |  |  |  |  |  |
| Clinician | X | X |  |  |  |  |
| Parent-Guardian |  | X |  |  |  |  |
| Biological Samples |  |  |  |  |  |  |
| Urine Sample | X | X |  |  |  |  |
| Blood Sample^6^ | X | X | X | X |  |  |
| Wound Fluid | X | X^7^ |  |  |  |  |
| Hair Sample | X |  |  |  | X |  |

COD = change of dressing; FLACC = face, legs, activity, cry, consolability; NRS = numeric rating scale; FACES = faces pain scale – revised

^1^ Every change of dressing until patient is 95% re-epithelialised.

^2^ Wound photos to be taken after debridement but before dressing application.

^3^ FLACC to be collected if patient under 7 years of age, NRS to be collected if patient ages 7 or over.

^4^ Patient pain scales only required for patients aged 7 years or older.

^5^ Implementation outcomes only required for patients enrolled in the intervention arm.

^6^ Only if patient is already cannulated or undergoing procedure under a general anaesthetic.

^7^ Only if patient in intervention arm and wound fluid able to be collected from NPWT device tubing.

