***Secondary Patient Outcomes:***

1. *Healing outcomes:* i) Time/days to re-epithelialisation (blinded photo assessment), ii) skin grafting requirements, iii) burn wound exudate, iv) number of dressing changes, v) adverse events (26).
2. *Operating theatre requirements:* i) proportion patients requiring an operation (%), ii) operations required per patient, iii) operative procedures performed (e.g., skin graft) (26).
3. *Hospital requirements 12 months post-injury:* i) proportion of patients needing ≥1 admissions to hospital (% & length of stay), ii) number of outpatient appointments, iii) number of scar clinic appointments.
4. *NPWT device malfunctions:* i) alarms ii) charging issues

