**8.4.2 Data Collection**

Research Nurses (ReNs) will collect primary and secondary outcome data prospectively by a combination of observation of, clinical staff, and patients/carers and electronic medical records (EMRs), using methods from previous studies (14, 41). Patient demographic and clinical characteristics will be recorded at initial presentation to the ED or burns service via EMR. Wound photos will be taken with a study iPad at each dressing change and deidentified for blinded review to assess and establish time to healing. ReNs will collect hospital data interactions (such as outpatient appointments, planned or unplanned return to ED, operating theatre and admission requirements) from each patient for 12 months post injury. Where possible burn wound exudate will be collected at NPWT application and removal and will be analysed using previous techniques (31) and related to the healing outcomes, to identify biological and biochemical mechanisms (42). ReNs will capture site level measures (e.g., ratios of burns treatment complications). The schedule of assessments for the trial is presented in Appendix 5.

Data will be directly entered by ReNs into a REDCap database (Research Electronic Data Capture, Vanderbilt, USA, hosted at Griffith University) using password-protected iPads. Identifying information will only be stored at the site level. Patient questionnaires will be completed over the telephone by an alternative site ReN (who is blinded to the crossover schedules) at three months post burn injury. We will instruct patients not to disclose their allocation (control or INPREP) to the ReN. Staff web-based questionnaires will be sent out 4 weeks into implementation and at completion of implementation phase. ReNs will conduct CFIR-informed clinician observations, interviews, and document analysis at each participating site.

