- Time to re-epithelialisation (days) will be examined using blinded photo assessment of patient’s injuries. Wounds will be photographed by the ReNs, using the study iPad, at each dressing change until the wound is considered 95% re-epithelialised by the child’s treating clinician at the site, and the wound no longer requires definitive silver dressings. A panel of burn experts (comprising of paediatric surgical consultants and experienced burns nurses) will perform a blinded review of patient’s photographed burn wounds – assessing if wounds are 95% re-epithelialised. Photos will be taken of patient’s burn injuries by the ReN at each follow up dressing change appointments This method has previously been used in recent trials assessing time to re-epithelialisation in paediatric burn patients (14, 41).
- Proportion of paediatric burn patients who require a skin graft for their injuries (rate of skin grafting), as well as adverse events (AE) and referrals to scar management will be documented in this investigation. The number, and type, of dressing changes until wound closure will also be recorded for all patients via observation and electronic medical record assessment.
- Biological molecules associated with healing (e.g., inflammatory markers, extracellular matrix production or remodelling, skin cell growth) will be assessed using wound exudate analysis. Any wound fluid able to be collected at NPWT application and removal will be analysed using previous techniques (31, 43) and related to the healing outcomes, to identify biological and biochemical mechanisms associated with wound healing or scarring (42).

*Wound Exudate Collection:*

Wound exudate will be collected from the participants during routine wound cleaning procedures. Instead of being discarded, the burn wound exudate will be retained and stored using the Standard Operating Procedure SOP-Wound-Fluid (see Appendix 1). Filter paper will be placed at the edge of the burn wound to absorb the wound exudate (44, 45). A comprehensive mass spectrometry (MS) analysis is possible from biological samples collected on paper (46). Researchers at the QCH site have previous experience collecting wound exudate from NPWT devices (43) and directly from the wound (47), and identifying proteins in these samples (31). Briefly, samples will be centrifuged to pellet cell debris and the supernatant will be aliquoted into tubes. Samples will be stored at -80C in a research facility or hospital laboratory at each site.

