**15. SIGNIFICANCE**

Not only will this study achieve the goals of the clinical partner (such as embedding evidence-based care and improving patient outcomes), but this study will also inform policy and practice nationally on how NPWT for children with acute burns can be implemented into various contexts of burn care. Whilst significant morbidity still exists for children with burns, innovative, cost effective, and sustainable solutions are required to decrease healing time and decrease the risk of scarring. This funding application provides a practical solution to a national problem. Evidence generated will inform paediatric burn care internationally. Through rigorous implementation methodology, this project will impact and sustain the INPREP Pathway beyond the funded study. This project will be the world’s first large-scale study to evaluate the implementation of NPWT for paediatric burns. Other key project outcomes will include:

- 1. Map of Australian acute paediatric burn care models of care and co-designed INPREP Pathway to nest within it
  2. Evidence-based implementation strategies
  3. Improved patient outcomes
  4. Identification of the biological and biochemical mechanisms underpinning the effectiveness of NPWT on acute burn wounds
  5. Development and distribution of education/training resources
  6. Cost-effective implementation
  7. Standardisation (sensitive to context)
  8. Comprehensive dissemination using innovative and diverse approaches via our website, training packages, social media/podcasts, webinars to implement NPWT and achieve benefits broadly and sustainably

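### Wound fluid at the first dressing change is scheduled only from NPWT tubing in the intervention arm, so an NPWT effect on exudate cannot be separated from time since burn or collection route

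*Protocol*

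**What the plan says.** Section 8.3.2 lists exudate among the healing outcomes: "iii) burn wound exudate". Section 12.2 says its models will compare usual care with INPREP on primary and secondary outcomes. Section 15 (Significance) names as a project output: "Identification of the biological and biochemical mechanisms underpinning the effectiveness of NPWT on acute burn wounds".

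The Appendix 5 row reads "Wound Fluid | X | X^7": one sample at initial presentation with no arm restriction, and one at COD1 under footnote 7, "Only if patient in intervention arm and wound fluid able to be collected from NPWT device tubing". The cells for later dressing changes, surgery, 3 months and 12 months are empty. In the same table, urine and blood at COD1 carry no arm restriction.

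The body text ties timing to the device as well. Section 8.4.2 says: "Where possible burn wound exudate will be collected at NPWT application and removal and will be analysed using previous techniques (31". The Healing outcomes subsection (8.4.4.2) uses the same two time points.

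Two places are worded more broadly. Section 8.4.4.2 also says "Wound exudate will be collected from the participants during routine wound cleaning procedures", and describes filter paper at the wound edge. The SOP in Appendix 1 covers blister fluid, exudating wounds and tubing fluid, and adds: "If there is only a small amount of fluid, this can be collected with filter paper". Neither names a follow-up visit for a child without NPWT.

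**The concern.** A mechanistic claim about NPWT needs post-treatment fluid from children who had NPWT and from comparable children who did not, taken at a similar time and in a similar way. As scheduled, the second group does not exist. Inflammatory and protease content may change over the first days of any burn, and fluid drawn through device tubing may differ from fluid taken at the wound edge or from a blister. If these proteins rise or fall between presentation and COD1 in NPWT-treated children, nothing collected in the trial shows whether the same would have happened under silver dressings.

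The general commitment in section 12.2 also cannot be met for post-treatment exudate. The only exudate contrast between phases is at presentation, before treatment. A later analysis plan cannot repair this, because the missing samples will not have been taken.

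**Working it through.** The plan states no figure on this point, so there is none to reproduce. The check is whether the scheduled samples can identify an NPWT effect.

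**Inputs.** Appendix 5 with footnote 7 gives three kinds of sample. The columns are indicators: COD1 rather than presentation, exposed to NPWT, and collected through tubing.

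| Sample | Intercept | Phase | COD1 | NPWT | Tubing |
|---|---|---|---|---|---|
| Control, presentation | 1 | 0 | 0 | 0 | 0 |
| Intervention, presentation | 1 | 1 | 0 | 0 | 0 |
| Intervention, COD1 | 1 | 1 | 1 | 1 | 1 |

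**Assumptions.** Presentation samples precede NPWT and do not come through tubing. Appendix 1 does allow for a child who arrives with a device attached; such a sample would still come through tubing and would add no untreated COD1 child. Visit stands in for time since burn.

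**Result as scheduled.** The COD1, NPWT and tubing columns are identical. With intercept, phase, COD1 and NPWT the matrix has rank 3 for 4 terms. With tubing added it has rank 3 for 5 terms. The difference between the second and third rows is the sum of the time, device and route effects, and only that sum can be estimated.

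**Adding control-phase COD1 samples by filter paper**, row (1, 0, 1, 0, 0): rank becomes 4 of 4, so NPWT separates from time. With tubing included it is 4 of 5: route is still confounded with NPWT.

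**Also sampling NPWT-treated children at COD1 by filter paper**, row (1, 1, 1, 1, 0): rank becomes 5 of 5. Device, time and route are then separable in this additive model.

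**Counts.** Control-phase COD1 samples: 0, whatever the recruitment. Footnote 7 also rules out implementation-phase children who do not receive NPWT (no tubing) and control-phase children who do (wrong arm), so no untreated comparator arises by chance.

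**The case against.** The strongest case on the other side has five parts.

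1. **The texts do not flatly conflict.** A reader might infer that footnote 7 contradicts section 8.4.4.2 and Appendix 1. It does not: sections 8.4.2 and 8.4.4.2 themselves tie collection to the device, the routine-cleaning sentence names no visit and is satisfied by the presentation sample, and Appendix 1 sets no follow-up visit. The broader wording needs aligning. This stands.
2. **The exudate outcome is not lost.** Sections 8.4.2 and 8.4.4.2 say the fluid will be related to healing. That can be done within NPWT-treated children, and presentation samples from both phases can be described. This stands. It yields markers associated with healing, however, and does not show what NPWT changed. The box of earlier studies after section 2.3 describes a comparison of NPWT fluid with matched burn exudate; this schedule provides no such match at COD1.
3. **The size is easily overstated.** A reader might take the minimum of 400 children, halve it, apply the 20% and 10% rates in section 12.1, and conclude at most 200 × 0.20 = 40 intervention samples, with 200 × 0.10 = 20 NPWT-treated controls lost. The documents do not support this. Those rates are adherence, which section 8.3.1 defines by eligibility and duration, so a child treated too briefly may be non-adherent yet still yield tubing fluid. The 100 per site is a minimum, at least 120 are anticipated, and the split between phases is not given.
4. **Untreated children are not automatically good comparators.** Section 8.4 leaves definitive care to treating clinicians, so NPWT use may follow severity. Adjusting an as-treated contrast for hours since burn alone would not remove that. This stands and shapes the fix.
5. **The item is minor.** Collection is opportunistic, in a trial whose primary outcome is adherence, and the documents do not show how much fluid can be recovered under silver dressings at COD1. This limits the weight of the point. Opportunistic sampling accounts for some missing samples; it does not account for a rule that excludes a whole phase.

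**Conclusion.** The point holds in this form. Under Appendix 5, and consistently with the device-based timing in sections 8.4.2 and 8.4.4.2, no child without NPWT gives a post-treatment wound fluid sample. An NPWT effect on exudate is fully confounded with visit and with collection route, and the only between-phase contrast is at presentation. The zero for control-phase COD1 samples follows from the rule and rests on no assumption about recruitment or adherence. No upper limit for the intervention side can be derived.

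The conclusion assumes that footnote 7 is applied as written and that presentation samples precede NPWT. Children who present late might give some untreated fluid at later hours after the burn, but the documents say nothing of their number, and the route would still differ. What is lost is attribution of post-treatment change to NPWT. This is worth correcting before sampling, because it cannot be corrected afterwards, but it concerns a secondary mechanistic outcome only.

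**What to change.** - Reword footnote 7 so that, at COD1, wound fluid is collected opportunistically from consenting children in both phases, whatever dressing was used, by the wound-edge filter-paper method already in section 8.4.4.2 and Appendix 1.
- Keep NPWT tubing fluid as an additional sample, and record the source of every sample.
- Align the timing sentences in sections 8.4.2 and 8.4.4.2 with the reworded footnote.
- State the comparison: like sample types at COD1, by randomised phase first, adjusted for time since burn, period, and the covariates in section 12.2 (total body surface area, age, gender).
- Report NPWT versus no NPWT as a secondary, non-randomised comparison that also adjusts for recorded severity such as burn depth. Use the assessment at presentation, since the re-assessment scheduled at COD1 comes after treatment has started.

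Cost: one footnote and two sentences to edit, plus filter paper, tubes, freezer space, aliquots and assays for the added samples. Section 8.4.3 already describes keeping fluid removed at routine cleaning that would otherwise be discarded, so no new procedure is introduced. Some control wounds may yield too little fluid; recording how often would itself be useful.
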